### 3.8. Outcome Evaluation

The primary effectiveness of the outcome will be evaluated by changes in the SBP and DBP of the patients from baseline to final follow-up at 12 months post-intervention. The secondary outcome measures will include (1) BP controlled to target (SBP < 140 mmHg and DBP < 90 mmHg); (2) composite outcome of death (all-cause) or hospital admission due to CHD, heart failure, or stroke; (3) incremental cost per HRQoL gained from baseline to end of follow-up; (4) improvement in the knowledge of patients on healthy lifestyle; (5) change in dietary salt intake; (6) change in quality of life; (7) change in the prevalence of current smokers; and (8) the treatment adherence rate. Hypertensive patients with poor adherence to their treatment regimens experience uncontrolled blood pressure. Adherence to hypertension treatment is defined as following the treatment regimen agreed to with their physician. According to the previous literature [29,30,31], a reduction of 5 mmHg of SBP is considered clinically relevant as it has been found to be significantly associated with a risk reduction in CHD, stroke, and other serious cardiovascular events. Health service utilization parameters will include the number and reason for visits to physicians and hospital admission, and when further complicated, the death of the patient. The cost-effectiveness measures are incremental cost per mmHg BP reduction or cost per HRQoL gained from baseline to end of follow-up at 12 months. For determining dietary salt intake level, a 24 h urinary sodium measurement will be opted.

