### 3.13. Statistical Analysis

All outcomes will be analyzed using the intention-to-treat principle. Descriptive statistics will be used to present baseline characteristics and outcome variables. Percentages and frequencies will be used for categorical variables, and means and standard deviations will be used for continuous variables. Baseline characteristics between the two arms will be compared with chi-square or Fisher’s exact test, as appropriate. A multilevel mixed model will be used to compare the differential changes in each outcome across the time points (T1, T3, and T5) to measure the primary and secondary outcomes. We will analyze group changes (with individual pharmacies treated as a random effect) using multivariable mixed linear and non-linear regression for normally and non-normally distributed data to account for the cluster randomization effects. Point estimates from cluster-adjusted models will be reported with 95% confidence intervals. Additionally, subgroup analysis will stratify data based on hypertension-related complications and the number of associated medications to estimate the effect of the interventions. For all two-tailed statistical tests, *p*-value < 0.05 will be considered statistically significant. We will perform all statistical analyses using R (version 4.1) and Stata software (version 17.0).

A cost-effectiveness analysis will be performed on the average total cost incurred in both arms, and incremental cost-effectiveness ratios expressed as incremental cost per (1) 1, 5, or 10 unit (mmHg) decrease in blood pressure; (2) one hospital admission reduced; (3) 1 day of hospital stay reduced over the previous 6 months among the survivors; and (4) HRQoL using data from EQ-5D-5L and mortality. We will calculate all cost data in US dollars, using the non-subsidized cost as of the study’s commencement.

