## 4. Discussion

This study protocol is developed as a quantitative approach to illustrate the feasibility of implementing a pharmacy-based health promotion program in South Asian community settings. The study aims to assess the impact and cost-effectiveness of education and counseling by CPs for controlling BP and promoting healthy lifestyle behavior among hypertensive individuals.

The evidence generated from this study is expected to aid in affirming the role of CPs as an integral part of primary care services to maximize the quality of provided care and match the specific needs of people in Bangladesh and Pakistan. CPs will be more confident in recognizing inadequate hypertension knowledge and medication adherence, and at-risk patients in the future. This will not only reinforce their role in improving the healthcare system but also lead to superior hypertensive patient outcomes.

This study will also exert significant impacts on hypertensive individuals, the community, and the healthcare system through the improved knowledge, healthier lifestyle choices, and capacity building of the CP to fill the gap in primary healthcare services. It is envisioned that pharmacies would become a central one-stop point in the community to retrieve hypertension-related information and management and obtain support among patients and caregivers. Apart from health and well-being, this study is anticipated to strengthen the patient–provider relationship between CPs and the community, which will be beneficial for tackling other chronic and communicable diseases. Lastly, with the decline in the rates of hypertension-related complications, non-adherence to medication, and hospitalization, the burden of the consequent cost of care will also be reduced. The study findings will thereby provide evidence on its sustainability and monetary value and hence inform stakeholders’ decisions in integrating this cost-effective model into the current community healthcare services.

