** *Baseline characteristics (Control and intervention group)* **												
Sociodemographic profile						x			x			x
Dietary habits						x			x			x
Physical exercise habits						x			x			x
Knowledge of hypertension						x			x			x
Direct treatment cost information						x			x			x
Indirect treatment cost information						x			x			x
HRQoL (EuroQoL-5D)						x			x			x

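### Section 3.13 builds the cost-effectiveness ratios on arm-average cost and does not link them to the pharmacy-adjusted, baseline-inclusive model stated for the other outcomes

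*Protocol article*

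**What the plan says.** The second paragraph of section 3.13 of the protocol article sets out the economic analysis: "A cost-effectiveness analysis will be performed on the average total cost incurred in both arms", with "incremental cost-effectiveness ratios expressed as incremental cost per (1) 1, 5, or 10 unit (mmHg) decrease in blood pressure". Three further denominators follow: a hospital admission avoided, a hospital day avoided, and HRQoL. The paragraph gives no covariate, cluster term or interval for cost.

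The first paragraph of the same section is more specific about the outcomes. It says "A multilevel mixed model will be used to compare the differential changes in each outcome across the time points (T1, T3, and T5"), T1 being month 0 in Table 2. Group changes are analysed "with individual pharmacies treated as a random effect", and "Point estimates from cluster-adjusted models will be reported with 95% confidence intervals". This model is meant for the primary and secondary outcomes, and section 3.8 counts "incremental cost per HRQoL gained from baseline to end of follow-up" among the secondary ones. Table 2 also lists cost per unit of BP reduction there.

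Table 2 marks "Direct treatment cost information", its indirect counterpart and the EuroQol measure at months 0, 6 and 12 for both arms. Section 2.2 makes value for money in public spending part of the study's objectives.

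**The concern.** The two paragraphs of section 3.13 treat cost and effect differently without saying so. The effect side has a stated estimator that includes the month-0 measurement and respects the unit of randomisation. The cost side has a mean per arm, put into a ratio.

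Two separate things are at stake, and they should not be merged:

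- **Precision.** A patient's treatment cost at month 0 probably predicts later cost. If it is not used, chance cost differences between the randomised groups of pharmacies pass unreduced into the numerator of every ICER.
- **Stated uncertainty.** Costs of patients at one pharmacy may be correlated. The cost comparison has no interval, and one added later at patient level would be too narrow. With equal pharmacy sizes, clustering leaves the difference in means itself unchanged; only its standard error is affected.

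A ratio printed alone also hides its components. If either difference is negative, the reader cannot tell from the ratio whether the result is favourable.

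**Working it through.** **Inputs from the protocol article**
- Bangladesh: 2 subdistricts × 20 pharmacies = 40 pharmacies, about 90 patients each (section 3.1), so 40 × 90 = 3,600.
- Pharmacies are randomised 1:1 (section 3.3), hence 20 pharmacies and 1,800 patients per arm.
- Sample-size inputs: difference 4.65, SD 49.78, 80% power, 5% significance (section 3.1).
- The documents give no cost SD, cost ICC, correlation between month-0 and later cost, or ICER value. ICC and correlation below are therefore assumptions, shown as ranges.

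**1. The plan's own figure**

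n per arm = 2 × (1.960 + 0.842)² × 49.78² / 4.65² ≈ 1,800, or 3,600 in total. The stated size is reproduced exactly as an individually randomised comparison, with no design effect. This does not show how cost will be analysed. It does show that the one calculation in the article leaves clustering out, so the cost analysis should not rely on clustering being understood.

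**2. Clustering**

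Design effect = 1 + (90 − 1) × ICC. The standard error of the cost difference grows by its square root. A nominal 95% interval that ignored clustering would cover 2Φ(1.96/√DE) − 1.

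| Assumed cost ICC | Design effect | SE factor | Coverage if ignored |
|---|---|---|---|
| 0.01 | 1.89 | 1.37 | 85% |
| 0.02 | 2.78 | 1.67 | 76% |
| 0.05 | 5.45 | 2.33 | 60% |

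The last column is conditional: it describes a patient-level interval that the protocol does not propose.

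**3. Month-0 cost**

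Adjusting for a baseline value with correlation ρ multiplies the variance by 1 − ρ².

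| Assumed ρ | Variance cut | SE factor |
|---|---|---|
| 0.3 | 9% | 0.95 |
| 0.5 | 25% | 0.87 |
| 0.7 | 49% | 0.71 |

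This is an individual-level approximation. With pharmacies as clusters, the gain also depends on the correlation of pharmacy means, which is not known.

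**4. Both together**

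The half-width of a 95% interval for the cost difference, in units of the cost SD, is 1.96 × √(2/1,800 × DE × (1 − ρ²)). For ICC 0.02 it is 0.109 without month-0 cost and 0.094 with ρ = 0.5. For ICC 0.05 it is 0.152 and 0.132.

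**5. Reading a ratio without its parts**

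A cost difference of −10 with an effect of +5 gives −2, and so does +10 with −5. The first is better on both counts, the second worse on both. Among savings the order also reverses: −20 for 5 mmHg gives −4, while the better −20 for 10 mmHg gives −2. Printing the two differences removes the ambiguity.

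**The case against.** The strongest reply is that mean cost per arm names the quantity to be compared, not the estimator. The article nowhere says that costs are unadjusted. The mixed model, with month 0 and the pharmacy effect, is stated for all secondary outcomes, and cost per HRQoL gained is one of them. This stands in part: a reader might infer that the protocol excludes adjustment, and the text does not support that. But the reply does not close the gap. No patient has an ICER, so a patient-level mixed model cannot be fitted to it, and no model is named for cost itself. The two paragraphs still need to be joined.

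A reader might also infer that the protocol expects a net saving, because the Discussion says "the burden of the consequent cost of care will also be reduced". That sentence concerns the cost of care. It does not say that total cost falls once training, equipment, calls and pharmacist time are counted. A negative incremental cost is possible but is not a stated expectation.

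It is tempting, too, to call the admission ratio unstable because its denominator may be near zero. The article gives no admission rate, so this would rest on assumed inputs alone and is not part of the point.

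Finally, net benefit, threshold ranges and the handling of dominance are commonly left to an analysis or health-economics plan that is not shown. Their absence is no finding. The point rests on the method that section 3.13 does state.

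**Conclusion.** The concern holds in a limited form. Section 3.13 states a cost comparison by arm averages and ratios and leaves it unconnected to the model given for the other outcomes, although the month-0 data that such a model needs are collected in both arms. The direction of the loss is clear; the sizes in the brief depend wholly on an assumed correlation and an assumed cost ICC, with 1,800 patients per arm in equal pharmacies of 90. The clustering factor becomes an actual error only if someone computes a patient-level interval.

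This does not touch the blood-pressure comparison. It bears on the value-for-money objective in section 2.2, where a ratio without a valid interval could be read as firmer than it is.

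**What to change.** Amend the economic paragraph of section 3.13 to say that:

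- incremental cost is estimated from a patient-level model with arm, month-0 cost and a pharmacy random effect;
- incremental HRQoL is estimated likewise, with month-0 EQ-5D as covariate;
- the cost and effect differences are reported with cluster-adjusted 95% confidence intervals next to each ICER, so that a negative ratio is read from its components.

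Resampling whole pharmacies within arm is one way to obtain the intervals and keeps cost and effect paired. It suits the 20 pharmacies per arm in Bangladesh; the four in Pakistan are too few to support it alone.

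The prespecified ICERs should all still be reported, whatever their sign. Net benefit over a range of thresholds is optional.

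The price is a change of wording and a little more analysis work. No further data collection is involved.

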### 3.14. Ethical Approval and Dissemination

After obtaining ethical approval from Hitotsubashi University and informed consent from the participants, an equal number of participants will be recruited for the intervention and control groups. The participants will be informed about the strictly voluntary nature of their participation and the right to completely withdraw from the survey at any point, without needing to provide a reason or fearing any impact on their rights. They can refrain from answering any question if they feel uneasy. Participants will also be assured that their personal data will remain confidential at all stages, and their identification will not be disclosed. The study findings will be disseminated through local, national, and international conferences; multiple peer-reviewed journals; and reports to key stakeholders. Trial registration number: ClinicalTrials.gov NCT06148142. Registered on 27 November 2023. https://classic.clinicaltrials.gov/ct2/show/NCT06148142.

## 4. Discussion

This study protocol is developed as a quantitative approach to illustrate the feasibility of implementing a pharmacy-based health promotion program in South Asian community settings. The study aims to assess the impact and cost-effectiveness of education and counseling by CPs for controlling BP and promoting healthy lifestyle behavior among hypertensive individuals.

The evidence generated from this study is expected to aid in affirming the role of CPs as an integral part of primary care services to maximize the quality of provided care and match the specific needs of people in Bangladesh and Pakistan. CPs will be more confident in recognizing inadequate hypertension knowledge and medication adherence, and at-risk patients in the future. This will not only reinforce their role in improving the healthcare system but also lead to superior hypertensive patient outcomes.

This study will also exert significant impacts on hypertensive individuals, the community, and the healthcare system through the improved knowledge, healthier lifestyle choices, and capacity building of the CP to fill the gap in primary healthcare services. It is envisioned that pharmacies would become a central one-stop point in the community to retrieve hypertension-related information and management and obtain support among patients and caregivers. Apart from health and well-being, this study is anticipated to strengthen the patient–provider relationship between CPs and the community, which will be beneficial for tackling other chronic and communicable diseases. Lastly, with the decline in the rates of hypertension-related complications, non-adherence to medication, and hospitalization, the burden of the consequent cost of care will also be reduced. The study findings will thereby provide evidence on its sustainability and monetary value and hence inform stakeholders’ decisions in integrating this cost-effective model into the current community healthcare services.

## 5. Limitations

The main limitation could be the high dropout rate as patients may be too busy to attend an educational session, some might lose interest and discontinue during the study period, and some participants might miss their routine follow-up visits due to political unrest or any other unavoidable circumstance. Although the patients’ presence can never be guaranteed, the research team and the CP will try their best to contact and persuade patients to participate. Secondly, missing data can be an issue in this trial; however, the planned analyses will follow intent-to-treat methods to minimize bias from dropout over time. A repeated-measurement bias can also be expected as the same questionnaire will be used at both baseline and endline surveys. Finally, due to the short follow-up duration, the long-term benefits of this CP model may not be observed at length. Despite these limitations, the study findings can give a basis for improving the future care of hypertensive patients in primary healthcare facilities in South Asia.

## 6. Conclusions

Considering the positive outcomes of this study and the increasing number of pharmacists in South Asia, health policymakers and professional organizations in the near future can enact policies or regulations for CPs to offer these services effectively and continually. This will also provide evidence to further develop various CP-led innovative health services to streamline the referral systems more efficiently. Thus, strengthening the pillars of the community (i.e., primary health workforce) and developing such robust research evidence will not only ensure effective control of different health conditions but also reduce the burden of health expenditure in resource-poor settings.

## Figures and Tables

**Figure 1 healthcare-12-01402-f001:**
[figure not shown]
Study design and workflow, Bangladesh. HP, hypertensive patients; CP, community pharmacy.

**Table 1 healthcare-12-01402-t001:** Content of pharmacist-led counseling intervention.

	Contents	Description	Practical Application
1.	**Overview of hypertension**	The pharmacist will describe the basics of hypertension, the cause of hypertension, the risk factors of hypertension, and common symptoms of hypertension including the current global statistics on it.	Utilizing visual aids and statistics, pharmacists will provide a global perspective on hypertension to enhance patient understanding.
2.	**Complications of hypertension**	Pharmacists will describe the common health-related complications of hypertension.	By illustrating potential health outcomes, pharmacists will emphasize the importance of hypertension management.
3.	**Impact of hypertension on family’s healthcare expenditure**	The pharmacist will inform the participants how uncontrolled hypertension may increase the disease burden as well as contribute to increasing the total family’s healthcare expenditure.	Through examples and case studies, pharmacists will show the economic impact on families to encourage adherence to treatment plans.
4.	**Management of hypertension**	The pharmacist will inform the patients about the general and clinical management of hypertension.	Pharmacists will use guidelines and protocols to educate patients on effective hypertension management practices.
5.	**Importance of lifestyle modification**	The pharmacist will discuss lifestyle modifications in hypertension management with the participants, which will include cessation of smoking, reducing alcohol intake, maintaining body weight, reducing and managing mental stress, and performing physical activity regularly.	Interactive sessions and personalized plans will be used to help patients adopt healthier lifestyles.
6.	**Importance of medication adherence**	In this part, the pharmacist will advise the participants regarding the consequences of poor adherence to antihypertensive medication and how it reduces the ultimate clinical outcome.	Pharmacists will provide strategies to improve medication adherence, such as setting reminders and creating a medication schedule.
7.	**Importance of food habit on hypertension control**	The pharmacist will inform the patients how food habits impact hypertension control, which will include avoiding extra salt consumption in meals, avoiding saturated fat and trans fats, much intake of food and vegetables, etc.	Diet plans and nutritional counseling will be provided to help patients make healthier food choices.
8.	**Importance of regular blood pressure measurement on hypertension control**	The pharmacist will suggest to the participants the significance of timely blood pressure monitoring and how it helps a person become more aware of their body. Also, they will suggest how blood pressure measuring assists a doctor in making a quick diagnosis of a health issue.	Demonstrations on how to properly measure BP and track readings will be conducted to empower patients to monitor their health.

**Table 2 healthcare-12-01402-t002:** Outcome measures and data collection time points.

	Screening, Enrollment and Randomization					Baseline	Follow-Up					Closed
	Wk 1	Wk 2	Wk 3	Wk 4	Wk 5	Month 0 (T1)	Month 3 (T2)		Month 6 (T3)	Month 9 (T4)		Month 12 (T5)
** *Assessment and intervention* **												
Selection criteria	x	x	x	x								
Informed consent	x	x	x	x								
Randomization					x							
Allocation					x							
** *Physical examination (Control and intervention group)* **												
Blood pressure measurement						x			x			x
BMI						x			x			x
Blood glucose measurement						x			x			x
** *Baseline characteristics (Control and intervention group)* **												
Sociodemographic profile						x			x			x
Dietary habits						x			x			x
Physical exercise habits						x			x			x
Knowledge of hypertension						x			x			x
Direct treatment cost information						x			x			x
Indirect treatment cost information						x			x			x
HRQoL (EuroQoL-5D)						x			x			x
** *Intervention criteria (Only intervention group)* **												
Audio–visual presentation						x			x			
Booklet distribution						x						
Phone call intervention							x			x		
** *Outcome measurements (Control and intervention group)* **												
*Primary outcome*												
Change in SBP and DBP									x			x
*Secondary outcome*												
BP controlled to target									x			x
Composite outcome of death or hospital admission									x			x
Improvement in knowledge									x			x
Changes in lifestyle									x			x
Changes in drug adherence									x			x
HRQoL gained									x			x
Cost per unit of BP reduction									x			x
Cost per HRQoL gained									x			x

HRQoL, health-related quality of life; SBP, systolic blood pressure; DBP, diastolic blood pressure; BP, blood pressure.

## Data Availability

The data follow the Guidelines for Accurate and Transparent Health Estimates Reporting. Requests for data-sharing will be considered by the corresponding author.
